# LOCAT (low-dose computed tomography for appendicitis trial) comparing clinical outcomes following low- vs standard-dose computed tomography as the first-line imaging test in adolescents and young adults with suspected acute appendicitis: study protocol for a randomized controlled trial

**DOI:** 10.1186/1745-6215-15-28

**Published:** 2014-01-17

**Keywords:** Appendicitis, Tomography, X-ray computed, Radiation

## Abstract

**Background:**

Computed tomography is widely used to diagnose acute appendicitis. Many adolescents and young adults are exposed to the associated radiation. A recent single-institution trial has reported promising results for low-dose computed tomography; however, this technique has not yet been widely adopted. LOCAT (low-dose computed tomography for appendicitis trial), a multi-institution randomized controlled non-inferiority trial, aims to compare low-dose computed tomography and standard-dose computed tomography as the first-line imaging tests for adolescents and young adults, and therefore to test the generalizability of the previous single-institution trial results.

**Methods/Design:**

Participants with suspected appendicitis are randomly assigned to either the low-dose group (with a typical effective dose of 2 mSv) or the standard-dose group (as used in normal practice at each participating site, typically 8 mSv). The primary end point is the negative appendectomy rate (the percentage of the number of uninflamed appendices that were removed among all non-incidental appendectomies), which is a consequence of false-positive diagnoses, with a non-inferiority margin of 4.5 percentage points. The key secondary end point is the appendiceal perforation rate, which is a consequence of delayed (or false-negative) diagnoses. Participant recruitment will be continued until the number of non-incidental appendectomies for each group exceeds 444. The total number of expected participants approximates 3,000, including those not undergoing appendectomy.

**Discussion:**

In addition to the study protocol, we elaborate on several challenging or potentially debatable components of the study design, including the broad eligibility criteria, choice of the primary end point, potential effect of using advanced imaging techniques on study results, determining and adjusting the radiation doses, ambiguities in reference standards, rationale for the non-inferiority margin, use of the intention-to-treat approach and difficulties in defining adverse events.

**Trial registration:**

ClinicalTrials.gov NCT01925014

## Background

Acute appendicitis is one of the most common indications for emergency abdominal surgery [1]. Computed tomography (CT) has assumed a paramount position in the disposition of adult patients with suspected appendicitis in the developed world, owing to its many advantages over other diagnostic tests including ultrasonography [2,3]. Studies conducted in Korea ([name] on behalf of the LOCAT group: Diagnostic imaging utilization in cases of acute appendicitis: multi-center experience, unpublished) and the United States [4-6] have reported preoperative CT utilization rates ranging from 93% to 98% in patients undergoing appendectomy between 2007 and 2011. CT is highly accurate, readily available, rapid, easy to perform and interpret, and rarely affected by bowel gas, severe abdominal pain or extreme body habitus [7]. Despite a historical debate [8], a number of recent studies [5,6,9-12] have consistently shown that the increased use of CT coincides with a reduction in the negative appendectomy rate (NAR) without an increase in the appendiceal perforation rate (APR). NAR is the percentage of the number of negative appendectomies (removal of an uninflamed appendix) out of all non-incidental appendectomies [6,8-12]. NAR and APR are two important reciprocal measures of the quality of care, indicative of false-positive and delayed (false-negative) diagnoses, respectively. The routine use of CT for patients suspected of having appendicitis has also been reported to be cost-effective through prevention of delayed or inaccurate diagnoses [13].

There has been a surge in CT use for diagnosing appendicitis during the last decade in the United States [5,6,8-12], indicating that the threshold for the decision to use CT may have declined. Over 250,000 appendectomies are performed in the United States each year [1], while approximately 95,000 were performed in the Republic of Korea in 2011 [14]. The vast majority of these patients undergo CT examination preoperatively [5,6,9,11,12]. Moreover, there is an even greater number of patients who undergo CT and do not finally undergo appendectomy. Factors contributing to these trends include improved CT technology, widespread availability, favorable reimbursement and a general shift in the culture of medicine toward defensive medicine [15] and dependency on imaging tests [16].

Many patients with suspected appendicitis are children or young adults [1], for whom CT radiation is of particular concern [17]. Although debatable, there are increasing concerns that even a single typical abdomen CT examination may increase the risk of carcinogenesis [17-19]. While such risk induced by an individual CT scan would be minute, multiplication by the large number of exposures may imply the real occurrence of cancer. With a greater awareness of the carcinogenic risk [19,20], it may no longer be certain if the benefits of CT in diagnosing appendicitis clearly outweigh the risk associated with the radiation doses traditionally used. It should be noted that the traditional radiation doses have historically been determined without robust scientific basis [21], with large variations in practice across hospitals [22]. Furthermore, while there is no rationale for using an identical dose for young appendicitis patients and elderly patients with malignancies, attempts have rarely been made to properly differentiate the dose levels according to the application.

Results from several studies have suggested that reducing the radiation dose by 50% to 80% does not significantly impair the diagnosis of appendicitis [23-25], although the dose reduction decreases image quality. Recently, a single-institution randomized controlled trial [26] demonstrated the non-inferiority of low-dose (LD) CT, which used a quarter of the standard dose (SD), compared to SD CT with respect to NAR (3.5% vs 3.2%; 95% CI for the difference, -3.8 to 4.6 percentage points) for adolescents and young adults with suspected appendicitis. However, the study had a potentially important limitation. While appendicitis is a very common disease encountered across emergency departments worldwide, it remains uncertain if the results of that particular study can be generalized to other institutions that are less experienced in using LD CT. At the time of writing, the LD CT technique has not been widely accepted as the standard of practice in many institutions. We have therefore proposed a multi-institution trial with a similar study design to confirm the generalizability of the results of the previous single-institution study. In this article, we summarize the protocol of the study, LOCAT (low-dose CT for appendicitis trial).

### Study objectives

The primary objective of LOCAT is to determine whether LD CT is non-inferior to SD CT as the first-line imaging test in regard to NAR for adolescents and young adults. In addition, LOCAT aims to disseminate the use of the LD CT technique throughout the participating sites through the implementation of the study protocol.

## Methods/design

### General

Conducting LOCAT at a site requires the approval of the site’s Institutional Review Board. LOCAT will be conducted in accordance with the Korean Good Clinical Practice Guideline [27]. Informed consent is a prerequisite. The protocol and the informed consent form should been approved by the ethics committee at each trial site (see Additional file 1).

LOCAT is a multi-institution single-blind randomized controlled non-inferiority trial comparing LD CT (with a typical effective dose of 2 mSv) and SD CT (as used in normal practice at each site) as the first-line imaging test for adolescents and young adults (Figure 1). The primary end point is the negative appendectomy rate and the key secondary end point is the appendiceal perforation rate. Participating radiologists are members of the Korean Society of Abdominal Radiology. LOCAT Group members are listed in Additional file 2. LOCAT was commissioned by the Korean Ministry of Health and Welfare in 2013, which is partly funding the study. Recruitment has commenced in December 2013.

**Figure 1 F1:**
[figure not shown]
Study overview.

### Eligibility criteria

Eligible patients are aged 15 to 44 years of age, visiting emergency departments with suspected symptoms and signs of acute appendicitis, undergoing intravenous contrast-enhanced CT examination requested due to suspicion of appendicitis, and without any prior cross-sectional imaging tests to evaluate the presenting symptoms and signs. Patients with a slender body shape, prior history of allergy to iodinated intravenous contrast materials or prior history of renal insufficiency will generally be recommended to undergo ultrasonography instead of CT, and therefore, are unlikely to be enrolled in LOCAT. However, these are not absolute exclusion criteria. To reproduce normal practice at each site, the clinical suspicion of appendicitis as well as the need for a CT examination will be left to the discretion of the emergency department physicians on duty.

The eligibility criteria differ from those in previous studies measuring the effect of preoperative CT on NAR [5,6,8-12] in that LOCAT participants are limited to adolescents and young adults for whom the long-term risks of cumulative radiation are more relevant [17].

### Site recruitment

The LOCAT office has been regularly sending out invitation letters to all members of the Korean Society of Abdominal Radiology (a nationwide society of abdominal radiologists), which has 303 members from 119 hospitals as of September 2013. As site recruitment is primarily based on the voluntary participation of radiologist investigators, the study’s generalizability may be limited. Before the first participant at a site is registered, the site must complete a checklist and rehearse the study procedures. The rehearsal includes all relevant study procedures, except that the rehearsal patients will undergo SD CT regardless of the results of the random assignment (sham randomization). Patients participating in the rehearsal will not be included in the sample size or final analyses.

### Randomization

Participants who give informed consent will be randomly assigned to either LD or SD CT at a 1:1 ratio. Details of stratification and blocks are confidential. Sequentially numbered opaque sealed envelopes containing computer-generated random assignments will be prepared for each site. Randomization will take place at the time of the CT examination. To enter a participant into LOCAT, the radiology technologist on duty will open the next consecutively numbered envelope.

While it is not possible to blind the medical staff to the allocation because of obvious differences in image texture (dependent on the CT radiation dose), the participants and independent outcome assessors will be kept blinded to the allocation.

### Diagnostic interventions

Single breath-hold intravenous contrast-enhanced helical scans are obtained during the portal venous phase using 16- or higher detector-row CT machines. The imaging parameters are listed in Table 1. An iterative reconstruction is strongly recommended particularly for LD CT. Otherwise, there is no restriction in regard to scanner type or scan parameters, and the imaging protocol should follow normal practice at each site. For each CT scanner, the radiation dose should be adjusted to give a predefined target dose-length product (DLP) for an average-size patient [28] for LD and SD CT. The actual radiation dose should be recorded, as it is automatically modulated according to the individual’s body size and shape [29].

**Table 1 T1:** CT imaging parameters

	**Imaging protocol**
Intravenous contrast enhancement	
Intravenous access	Antecubital, not lower extremity
Contrast material	Iodine, 400 to 800 mg/kg
Scan timing	Portal venous phase
Scan	
Range	From 4 cm above the liver dome to 1 cm below the ischial tuberosity
Collimation	Use all detector rows available
Automatic exposure control	Use all techniques available
Reconstruction	
Thick transverse images	Section thickness, 3 to 5 mm; overlap, 20% or more
Thin transverse images	Section thickness ≤2 mm; reconstruction interval ≤1 mm

The risk of cancer associated with the CT radiation for each group can be estimated using a method used in the previous single-institution trial [26]. According to the calculation in that trial, using SD CT (approximately 8 mSv) instead of LD CT (approximately 2 mSv) for 2,000 male or 1,800 female 30-year-old patients would result in one additional cancer.

#### LD CT

The target DLP is set at 130 mGy · cm, which corresponds to an effective dose of 2 mSv with a conversion factor of 0.015 mSv · mGy^–1^ · cm^–1^[30]. This ‘low’ dose was empirically determined based on experience in depicting the appendix using reduced tube currents [24,25,31]. It was subsequently used in the previous single-institution trial [26].

#### SD CT

For the SD group, the target DLP is left to the discretion of the site principal investigator (PI) in line with the normal practice at each site. The target DLP is typically 530 mGy · cm corresponding to 8 mSv, but should not exceed the typical dose used in normal practice at the site. In comparison, reference values often quoted at the time this article was written range from 7 to 10 mSv [32-34]. It should be noted that the site PI is allowed to change the target DLP for each CT machine for the SD group during the study period and that no lower limit is defined for the target DLP. This is because the “standard” dose used at each site may decrease gradually during the study period [35], as will be discussed later.

### CT image interpretation and radiologists

In daily clinical practice, site radiologists produce some CT reports by reviewing images using the multiplanar sliding slab averaging technique, a real-time image post-processing technique [36-38], which is widely used to review large thin-section CT datasets efficiently. Typically, the initial CT reports are made by attending radiologists during the daytime and by on-call radiologists after hours. The CT reports are produced using a predefined structured format. The likelihood of appendicitis is rated on a five-point Likert scale.

LD CT is less straightforward to interpret than SD CT due to the lower image quality. Furthermore, most radiologists have limited experience in using LD CT prior to joining LOCAT. Therefore, to ensure the safety of the participants, it is mandatory at a site that more than 80% of the radiologists potentially involved in CT interpretation should complete a self-learning course before the first participant at the site is registered. The training materials include introductory PowerPoint slideshows and LD CT cases selected from the previous single-institution study [26] with direct feedback for the appendix’s location and the final diagnosis.

### Additional imaging

If the diagnosis of appendicitis remains undetermined after the initial CT examination and clinical observation, then additional abdominal imaging test(s), including abdominal ultrasonography [39,40] or SD CT, can be performed at the discretion of the emergency department physician or surgeon. An additional imaging test is defined as one that is performed within 7 days of the initial CT to diagnose or rule out appendicitis.

### Primary end point

The primary end point is NAR. As a secondary analysis, an alternative definition of NAR is used, which excludes cases with appendiceal neoplasms without superimposed appendicitis, as appendectomy would be indicated for such patients ([name] on behalf of the LOCAT group: Diagnostic imaging utilization in cases of acute appendicitis: multi-center experience, unpublished). Any surgery performed for the treatment of presumed appendicitis is counted as non-incidental appendectomy, even though the surgical procedures may be more extensive than simple appendectomy (for example, ileocecectomy).

### Important secondary end points

#### Clinical outcomes

• APR, defined as the percentage of the number of perforated appendicitis for all confirmed appendicitis cases [8-11]

• The proportion of patients requiring additional imaging test(s) to diagnose or rule out appendicitis

• Delay in patient disposition

 ➢ Interval from CT acquisition to appendectomy in patients undergoing non-incidental appendectomy

 ➢ Interval from CT acquisition to hospital discharge in patients not undergoing surgery

• Length of hospital stay associated with non-incidental appendectomy, defined as the interval from CT acquisition to hospital discharge after non-incidental appendectomy

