#### Radiologic outcomes for the diagnosis of appendicitis

• Diagnostic performance

 ➢ Area under receiver-operating-characteristic curve

• Diagnostic confidence

 ➢ Likelihood score for appendicitis in patients confirmed as having appendicitis

 ➢ Likelihood score for appendicitis in patients confirmed as not having appendicitis

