### Reference standards

For participants undergoing abdominal surgery, the final diagnosis is made using the surgical and pathologic findings. Pathologic examinations of surgical specimens are performed by site pathologists during daily practice [41]. For participants not undergoing surgery, the outcome assessors will determine the final diagnosis based on the medical records and a standardized telephone interview conducted 3 months after the initial presentation. The outcome assessors are emergency department physicians or radiologists blinded to the allocation.

The histopathologic diagnosis of acute appendicitis is defined as neutrophil infiltration of the appendiceal wall [41]. If neutrophilic collections are confined to the mucosa, the diagnosis of acute appendicitis is based on the presence of mucosal ulcerations [42]. A diagnosis of appendiceal perforation is based on spillage of the appendiceal contents, peritonitis or an abscess observed during surgery [43], or a pathologically confirmed appendiceal wall defect due to transmural necrosis.

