### Analysis

All participants undergoing randomization will be included in the analysis in the groups to which they are originally assigned. While the intention-to-treat analysis will be used primarily, an additional per-protocol analysis will be performed. The NARs for both groups and the two-sided 95% CI for the differences will be calculated. The non-inferiority of LD CT compared to SD CT will be accepted if the upper bound of the two-sided 95% CI lies below the non-inferiority margin, which is 4.5 percentage points.

A similar non-inferiority analysis will be performed for APR with a non-inferiority margin of 10.0 percentage points. Chi-square tests, Fisher’s exact tests, Mann–Whitney U tests and receiver-operating-characteristic analysis (non-parametric Wilcoxon statistic) will be used to compare the other secondary end points. A two-sided *P* < 0.05 indicates statistical significance. If the study results show considerable variation across sites, generalized estimating equations will be used to account for the clustering effect by site.

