### Potential ambiguities in reference standards

The pathologic diagnosis of appendicitis is not always straightforward when inflammation is confined to the mucosa. A systematic review [47] found that the pathologic criteria for appendicitis were missing or inconsistent in many previous studies. To ensure diagnostic reproducibility across the pathologists and sites, we have prepared a guideline.

The definition of appendiceal perforation is also unclear in previous studies addressing APR [8-11,59,60]. Importantly, in the previous studies it is particularly unclear whether appendiceal perforation refers only to a gross periappendiceal abscess or generalized peritonitis, or also includes microscopic perforation with localized peritonitis of minimal extent. While the former can alter the patient’s prognosis or the treatment plan, the latter is unlikely to do so. In LOCAT, the aforementioned broad definition is used to cover both extreme types.

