### Rationale for the non-inferiority margin

To justify the non-inferiority margin of 4.5 percentage points for NAR, we have summarized the previously reported NARs. Several previous studies found that there was a decrease in NAR from a range of 12% to 29% down to 3% to 11% with the introduction of preoperative CT, as reviewed by Coursey *et al*. [6]. According to more recent studies [5,6,11,26,60], which likely used modern CT scanners with radiation doses presumably similar to the SD in LOCAT, the reported NAR ranged from 3.0% to 8.2%. To our knowledge, there has been no randomized controlled trial demonstrating the efficacy or effectiveness of SD CT over a placebo (no CT), which could be used as the basis for statistical reasoning of the non-inferiority margin [61]. Instead, a meta-analysis [62] suggested a NAR of 16.7% without preoperative CT compared to 8.6% with preoperative CT. More recent large observational studies [4] reported NARs of 8.5% to 12% in patients who underwent preoperative ultrasonography instead of CT.

For the non-inferiority test for APR, we assume 25% APR following SD CT based on previous data (ranging from 23% to 31%) from some of the sites [24-26]. The same APR is assumed following LD CT. We judge 35% APR to be clinically acceptable following LD CT, which corresponds to a non-inferiority margin of 10 percentage points. With these assumptions and with the 10% dropout rate and 4% NAR, the sample size determined to conclude the non-inferiority in NAR, 444 non-incidental appendectomies per group, would have a power of 89% in concluding the non-inferiority in APR.

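### As worded, the appendiceal perforation rate can count non-operated appendicitis in its denominator but recognizes perforation only at surgery or on pathology, and its power calculation uses operated cases only

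*Protocol article*

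**What the plan says.** Four places in the protocol article bear on the appendiceal perforation rate (APR).

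- **Denominator.** Clinical outcomes, under Important secondary end points: "APR, defined as the percentage of the number of perforated appendicitis for all confirmed appendicitis cases". There is no restriction to operated cases, although other items in the same list are restricted explicitly by whether surgery took place.
- **How appendicitis is confirmed.** Reference standards: surgical and pathologic findings are used when there is an operation. Otherwise, "For participants not undergoing surgery, the outcome assessors will determine the final diagnosis based on the medical records and a standardized telephone interview", the interview being held 3 months after presentation.
- **Numerator.** Reference standards: "A diagnosis of appendiceal perforation is based on spillage of the appendiceal contents, peritonitis or an abscess observed during surgery", "or a pathologically confirmed appendiceal wall defect due to transmural necrosis". The Discussion section on ambiguities in reference standards distinguishes gross abscess or generalized peritonitis from microscopic perforation, and adds: "In LOCAT, the aforementioned broad definition is used to cover both extreme types".
- **Test and power.** Analysis: "A similar non-inferiority analysis will be performed for APR with a non-inferiority margin of 10.0 percentage points". The test follows the negative appendectomy rate (NAR) in a fixed sequence. The power is given under Rationale for the non-inferiority margin: "With these assumptions and with the 10% dropout rate and 4% NAR, the sample size determined", that is 444 appendectomies per group, gives 89% at an assumed APR of 25% in both arms.

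**The concern.** A rate is interpretable only if everyone in the denominator could have entered the numerator. Here a participant whose appendicitis is confirmed from records and interview, who had an abscess and was never operated on, appears to add one to the denominator and nothing to the numerator. The abscess is then scored as absence of perforation, although the Discussion says that the definition is meant to reach gross abscess.

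APR is the article's measure of harm from delayed or false-negative diagnosis, and it carries a formal non-inferiority test with a 10-point margin. Whether a case can enter the numerator depends on a decision to operate, taken after randomization by staff whom the article says cannot be blinded. Equal non-operated shares in the two arms therefore cannot be taken for granted. If they differ, the comparison of arms is distorted.

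**Working it through.** **1. The plan's own figures.**

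NAR sample size, with 4% in both arms, margin 4.5 points, two-sided α 0.05 and power 90%:
n = (1.960 + 1.282)² × 2 × 0.04 × 0.96 / 0.045² = 398.5, so 399 per group. 399 / 0.90 = 443.3, so 444. This matches.

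APR power, with 25% in both arms and margin 10 points:
- n = 444 × 0.90 × 0.96 = 383.6 per group
- SE = √(2 × 0.25 × 0.75 / 383.6) = 0.03127
- power = Φ(0.10 / 0.03127 − 1.960) = Φ(1.238) = 89.2%, against the stated 89%

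The figure is sound. Its denominator is operated, inflamed appendices that remain after dropout. That is not the denominator in the end point's definition, unless confirmed is taken to mean confirmed at operation.

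**2. Effect within one arm.**

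Let x be the share of confirmed appendicitis managed without surgery and q the share of those with abscess or perforation. The document gives neither, so both are assumed. With 25% perforation among operated cases:
- APR as worded = 0.25(1 − x)
- APR over all confirmed cases = 0.25(1 − x) + qx
- shortfall = qx

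| x | APR as worded | All-case APR, q = 25% to 100% | Shortfall (points) |
|---|---|---|---|
| 2% | 24.5% | 25.0% to 26.5% | 0.5 to 2.0 |
| 5% | 23.75% | 25.0% to 28.75% | 1.25 to 5.0 |
| 10% | 22.5% | 25.0% to 32.5% | 2.5 to 10.0 |

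**3. Effect on the comparison, low dose (LD) minus standard dose (SD), operated APR 25% in both arms.**

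| x in SD | x in LD | q | As worded (points) | All-case (points) |
|---|---|---|---|---|
| 2% | 5% | 25% | −0.75 | 0.0 |
| 2% | 5% | 100% | −0.75 | +2.25 |
| 2% | 10% | 50% | −2.0 | +2.0 |
| 2% | 10% | 100% | −2.0 | +6.0 |

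Exchanging the arms reverses every sign. With the same x in both arms, a true difference among operated cases is only scaled by (1 − x): 10 points become 9.5 at x = 5%.

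**4. Would the decision change?**

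*Middle illustration.* Take 384 operated cases per arm with 96 perforated, plus 20 (SD) and 40 (LD) non-operated cases, all with abscess.
- As worded: 96/424 − 96/404 = 22.6% − 23.8% = −1.1 points, SE 2.94, 95% CI −6.9 to 4.6.
- All-case: 136/424 − 116/404 = 32.1% − 28.7% = +3.4 points, SE 3.19, 95% CI −2.9 to 9.6.

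The estimate moves by 4.5 points and changes sign, but both upper bounds lie below 10 and non-inferiority is declared either way.

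*Extreme row of the table* (2% against 10%, q = 100%). The denominators are 383.6/0.98 = 391.4 and 383.6/0.90 = 426.2.
- As worded: −2.0 points, SE 2.97, upper bound −2.0 + 1.96 × 2.97 = 3.8.
- All-case: +6.0 points, SE 3.18, upper bound 6.0 + 1.96 × 3.18 = 12.2, which fails the margin.

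The decision turns only under this fivefold imbalance with every non-operated case perforated. Nothing in the document supports those inputs.

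**The case against.** **Operated cases may be what was meant.** No section says outright that non-operated cases enter APR. The power calculation starts from appendectomies and removes the negative ones, and the perforation criteria are surgical or pathologic. Both suggest that confirmed means confirmed at operation. The radiologic end points also speak of confirmation ("Likelihood score for appendicitis in patients confirmed as not having appendicitis"), but that wording does not mention surgery, and those end points need a diagnosis for everyone, so it settles little. This is good evidence of intent. It does not remove the problem, because the definition as written says all confirmed cases and the reference standard lets a diagnosis be set without surgery. If operated cases were intended, the wording needs to say so, and non-operated abscesses then leave APR altogether.

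**A reader might infer that the APR test is biased toward non-inferiority.** The document does not support that. It requires more non-operated perforated cases in the LD arm. The article gives no such counts, and an excess in the SD arm would push the other way.

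**The surgical or pathologic criterion has a merit.** It does not depend on the randomized imaging. An abscess counted from the initial CT report would make the outcome depend on the test under comparison, and the article itself says LD images are harder to read. This stands and shapes the fix.

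**APR is secondary, its ambiguity is acknowledged, and the article is condensed.** All true, and they limit severity. But the acknowledged ambiguity concerns gross against microscopic perforation, not operated against non-operated cases. Nor is this a missing detail: both definitions are stated, and they do not fit together.

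**Conclusion.** The point holds as a mismatch between three statements: a denominator that can include non-operated cases, a numerator confined to surgical or pathologic findings, and a power calculation on operated cases. As worded, each non-operated confirmed case with an abscess lowers its arm's APR, by qx in total. That is 0.5 to 10 points over the assumed range x = 2% to 10% and q = 25% to 100%. The comparison between arms is distorted if such cases differ by arm, in a direction and by an amount that the document does not give.

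The 444 and the 89% are arithmetically correct. The primary NAR analysis is unaffected. Because APR is the key secondary end point with a formal test, the severity is moderate: worth correcting before analysis, but not a defect that undermines the trial.

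**What to change.** 1. Define the APR denominator as surgically or pathologically confirmed appendicitis. This matches the numerator and the population behind the 89% power.
2. Report the number of non-operated confirmed appendicitis cases in each arm, with the number that have a documented abscess or perforation.
3. Add a sensitivity analysis over all confirmed cases. The blinded assessors count a non-operated case as perforated when the records document an abscess or perforation, without relying on the randomized initial CT report alone.

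The cost is a change of wording and one extra field from records that the assessors already review. The downside is that the restricted APR leaves out non-operated perforations: in the 20 against 40 illustration it would show 96/384 in both arms, a difference of zero, while the all-case difference is +3.4 points. The sensitivity analysis is there to show such a gap and should be reported beside the main APR result.
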